## 1. SUMMARY

Pre-eclampsia is a multi-system syndrome of pregnancy characterised by hypertension and proteinuria. Early onset pre-eclampsia, prior to 32 weeks' gestation, is associated with substantial morbidity and mortality for both mother and baby. As yet there is no effective treatment for pre-eclampsia other than delivery of the baby.

Recent research has identified that the placenta releases factors (anti-angiogenic factors) into maternal blood before the onset of pre-eclampsia. Initial studies suggest that statins can reduce the level of these factors, and perhaps reduce or eliminate the effects of pre-eclampsia.

This trial aims to establish whether pravastatin causes a significant reduction of these placental factors in women with early-onset pre-eclampsia. To test this hypothesis, we will ask the following questions:

1. Does pravastatin cause a greater inhibition of circulating placental factors in women with early-onset pre-eclampsia compared with placebo?
2. Are there any adverse or beneficial effects to the mother or the baby following gestational exposure to pravastatin during pre-eclampsia?
3. If pravastatin appears to safely inhibit circulating placental factors, how best can a substantive trial/health technology assessment be undertaken to develop guidance for routine use of statins to prevent or ameliorate pre-eclampsia?

StAmP is a double blind, placebo controlled multicentre randomised trial of pravastatin to ameliorate early onset pre-eclampsia.

Early-onset pre-eclampsia affects 1:200 primigravid pregnancies. In order to obtain the number of patients necessary even for this proof of principle trial of statins for the amelioration of pre-eclampsia, the trial will need the participation of several centres. To make this practicable, trial procedures need to be kept simple, minimising the bureaucratic burden on participating clinicians, using simple randomisation procedures and centralised coordination of trial drug packs.

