## **6.6. Sample collection**

### **6.6.1. Blood sample collection**

Blood samples of 5-10mls will be collected for the analysis of inflammatory and anti-angiogenic factors including s-Flt-1, PlGF, and sENG. As a minimum, samples need to be collected daily at baseline, on days 1-3 of the trial treatment period and twice a week thereafter until discharge from hospital post-delivery. Blood samples should be taken at the same time as routine sampling wherever possible, however where this is not possible, additional samples may occasionally need to be taken specifically for the trial. All samples should be spun down and plasma collected. The plasma sample tube should be labelled with a pre-printed label containing StAmP Trial Number, sample day and type. Patient initials, date of birth and date of sample should be written on the label. Samples will be stored in a -80°C freezer (or -20°C if not available) within a StAmP sample storage box, until the mother has completed her involvement in the trial.

Once the mother has completed her involvement in the trial (after the 6-week post-partum blood sample collection), all tubes should be sealed and sent to Aston University as and when instructed by the StAmP Trial Office.

The StAmP Trial Office will send out instructions on sample preparation, freezing and transport guidelines to all participating centres.

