### 8.2. Secondary outcome measures

Secondary measures will be:

- The level of maternal circulating sFlt-1 and the ratio of sFlt-1 to PlGF over the first 14 days post-randomisation. Most women are expected to provide regular measurements before childbirth. Pregnancy with pre-eclampsia is expected to last for an average  $11\pm 5$  days, so estimates of effects over the first two weeks are expected to be from a largely complete set of data. All available data, both clinical and biochemical will be examined to see if this influences interpretation of results.
- Severity of pre-eclampsia as indicated by maternal blood pressure, level of proteinuria, platelet count, liver-transaminases, renal function, fetal biometry and umbilical artery blood flow 48 hours after randomisation and for the remainder of the pregnancy.
- Length of gestation post-randomisation, in days.
- Maternal morbidity, as indicated by serum creatinine  $\geq 120\mu\text{mol/L}$ , proteinuria  $\geq 5\text{g/24h}$ ; signs of left ventricular failure (pulmonary oedema, oxygen sats  $< 95\%$ ); hypertension  $\geq 170/110\text{mmHg}$  despite anti-hypertensive treatment; disseminated intravascular coagulation and/or platelets  $< 50 \times 10^9$ ; eclampsia; cerebrovascular event; liver transaminase  $\geq 500\text{IU/L}$ , more than 48 hours after randomisation and for the remainder of the pregnancy.
- Neonatal Apgar score at 1, 5, 10 minutes
- Use of anti-hypertensives
- Level of pravastatin in the cord blood at delivery relative to maternal levels.
- Serious adverse events and reactions

Secondary outcomes will be collected prior to randomisation, daily throughout pregnancy and at birth. The data items collected to identify secondary outcomes are shown in Table 1.

When analyzing secondary outcomes, length of gestation post randomization will be considered the most important indicator of potential clinical efficacy.

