| Liver transaminase                                                | X                      | X                           | X              | X                          | X                           |
| Total cholesterol                                                 | X                      | X                           | X              | X                          |                             |
| C-reactive protein                                                | X                      | X                           | X              | X                          |                             |
| Haematological Measures                                           |                        |                             |                |                            |                             |
| Heamoglobin                                                       | X                      | X                           | X              |                            |                             |
| Platelet count                                                    | X                      | X                           | X              | X                          | X                           |
| WCC                                                               | X                      | X                           | X              |                            |                             |
| Biomarkers                                                        |                        |                             |                |                            |                             |
| Plasma sFlt/ sEng/ PIGF                                           | X                      | X                           | X              | X                          | X                           |
| Anti-hypertensive/ other pre-eclampsia treatment                  | X                      | X                           | X              | X                          |                             |
| Maternal mortality/ morbidity                                     |                        | X                           | X              | X                          | X                           |
| Fetal & Neonatal Measures                                         |                        |                             |                |                            |                             |

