## **9.2. Statistical Analysis**

The primary outcome measure of sFlt-1 during the first three days will be analysed using a repeated measures analysis in SAS PROC MIXED, including the baseline value as a covariate. For the primary analysis the treatment effect will be considered constant over time, secondary analyses will examine the possibility of a trend over time. Plots of mean score over time will be shown for clarification.

As a secondary analysis sFlt-1 and the sFlt-1/PIGF ratio over, initially, the first 14 days and latterly all available data will be analysed using a repeated measures analysis in SAS PROC MIXED. Parameters allowing for treatment arm, time and baseline value will be included in the model. Initially, the treatment effect will be assumed to be constant over time, but if time by treatment interaction is shown to be important by including this parameter in the model (the conventional level of  $p = 0.05$  will be used here) then further investigation into effects at differing time points will be made by analysing the least-square means as above. Plots of mean score over time will be shown for clarification.

The length of gestation (to delivery) post randomisation will be analysed using a Cox Proportional Hazards model. Hazard ratios will be calculated. Kaplan-Meier plots will be produced.

All other continuous measures (clinical measures, etc) will be considered in the same manner as above (adjusting by baseline value if available). Dichotomous outcomes (mortality, etc) will be presented as risk ratios, with a corresponding chi-squared test performed. The latter will be analysed using SAS PROC GENMOD.

Apart from baseline value, no adjustments for covariates will be made in the first instance in any of the investigations above as good balance is expected between groups due to the minimisation procedure at randomisation.

All analysis will be by intention-to-treat, whereby patients will be analysed according to the arm they were randomised to regardless of whether they complied with the treatment. All tests are 2-sided and results will be presented as a point estimate along with 95% confidence intervals. All analyses will be conducted by the trial statistician at the BCTU. A comprehensive Statistical Analysis Plan will be drawn up prior to any analysis and will provide further details on the proposed analysis.

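### The secondary sFlt-1 and sFlt-1/PlGF analyses set no cut-off at delivery, so post-partum, off-drug samples can enter the treatment comparison

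*Combined protocol and SAP*

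**What the plan says.** - **Analysis (9.2).** The plan for the secondary biomarker analysis reads: "As a secondary analysis sFlt-1 and the sFlt-1/PIGF ratio over, initially, the first 14 days and latterly all available data will be analysed". The method is a repeated-measures model. On its terms, the section states: "Parameters allowing for treatment arm, time and baseline value will be included in the model". On the form of the effect, it adds: "Initially, the treatment effect will be assumed to be constant over time", with a time-by-treatment interaction then tested at p=0.05. Delivery is not mentioned as a cut-off, a covariate or a reason for missing data.
- **Sampling (6.6.1, Table 1, 8.3).** After day 3, blood is taken "twice a week thereafter until discharge from hospital post-delivery". The Table 1 row "Plasma sFlt/ sEng/ PIGF" is marked in all five columns, including child-birth, the period to discharge, and 6 weeks. Section 8.3 confirms that the 6-week sample is for biomarker assay.
- **Source and exposure (1, 6.2.2).** The Summary says that "the placenta releases factors (anti-angiogenic factors) into maternal blood". Section 6.2.2 ends treatment when the pregnancy ends.
- **Completeness (8.2).** The 14-day outcome is justified by an expected 11±5 days of continuing pregnancy, "so estimates of effects over the first two weeks are expected to be from a largely complete set of data". The preceding sentence there speaks of regular measurements before childbirth.
- **Delivery as an outcome (8.2).** Length of gestation after randomisation is ranked as the leading indicator of clinical efficacy among the secondary outcomes.
- **Missing data (9.2.1).** Sensitivity analyses based on multiple imputation are planned, with details left to a later SAP.

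**The concern.** A sample taken after delivery reflects loss of the placental source, off drug. Averaging it with on-treatment pregnancy values under one treatment term answers a mixed question. The mixture also need not be balanced: the proportion of post-delivery samples in each arm depends on when women deliver, which pravastatin is hoped to change. If it prolongs pregnancy, the placebo arm contributes more low post-partum values, and the comparison moves against pravastatin for a reason unrelated to its effect on sFlt-1.

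At stake are the first-listed secondary outcome and the only planned analysis of the sFlt-1/PlGF ratio, in a trial meant to inform a larger one (2.6).

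**Working it through.** **Inputs from the protocol.** Time to delivery 11±5 days (8.2; ± is unlabelled and read here as an SD). sFlt-1 in pre-eclampsia 66.6±26.4 ng/ml; in normal pregnancy 19.3 ng/ml; expected effect a halving (9.1). Up to 64 women. Samples on days 1-3, then twice weekly.

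**Assumptions, not in the documents.** The twice-weekly samples fall on days 6, 10 and 13. Postnatal stay s is 3-7 days. sFlt-1 drops at delivery to 10-19.3 ng/ml in both arms. Pravastatin prolongs pregnancy by 0 or 3 days. The true fall is 20 ng/ml (about 30% of 66.6).

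The plan gives no completeness percentage to reproduce. Its sample sizes of 34 and 32 concern the three-day primary analysis and have no bearing here.

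**Step 1: pre-delivery availability.** P(delivered by day t) = Φ((t−11)/5).
- Day 3: Φ(−1.6) = 5.5% (0.3-5.5% across normal, truncated normal, gamma and lognormal).
- Day 7: Φ(−0.8) = 21%, so about 50 of 64 women are still pregnant.
- Day 14: Φ(0.6) = 72.6% (72-78% across the four distributions), so 64 × 0.274 ≈ 18 are still pregnant (14-18 across distributions).
- Share of the 14-day woman-days spent pregnant, ∫S(t)dt/14 over 0-14, where S(t) is the proportion still pregnant at day t: 72-74%.
- Share of the six scheduled samples falling before delivery, normal model: (0.977+0.964+0.945+0.841+0.579+0.345)/6 = 0.775, about 78%. Coverage is nearly full to day 3 and poor by day 13.

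**Step 2: post-delivery share if nothing is excluded.** With F the distribution function of delivery time, p = Σ[F(d)−F(d−s)] / Σ[1−F(d−s)] over the sampling days d. With gamma times of mean 11 and SD 5, p is 12%, 17% and 20% for stays of 3, 5 and 7 days (27%, 36% and 41% of samples after day 3). On this reading 88-97% of scheduled samples would exist.

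**Step 3: effect on the comparison.** For a simple pooled difference in means, with p₀ and p₁ the placebo and pravastatin shares:
- apparent difference under a true null = (p₀−p₁) × (66.6−post-delivery level);
- apparent difference under a true 20 ng/ml fall = that amount − 20 × (1−p₁).

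The extremes of the range, gamma times:

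| Prolongation | Stay | Post level | p₀ | p₁ | True null appears as | True −20 appears as | Attenuation |
|---|---|---|---|---|---|---|---|
| 0 d | 3 d | either | 0.119 | 0.119 | 0 | −20×0.881 = −17.6 | 12% |
| 0 d | 7 d | either | 0.203 | 0.203 | 0 | −20×0.797 = −15.9 | 20% |
| 3 d | 3 d | 19.3 | 0.119 | 0.077 | 0.042×47.3 = +2.0 | 2.0−20×0.923 = −16.5 | 18% |
| 3 d | 7 d | 10 | 0.203 | 0.115 | 0.088×56.6 = +5.0 | 5.0−20×0.885 = −12.7 | 36% |

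Normal delivery times give results within or very close to these ranges. The null bias of +2 to +5 ng/ml is 0.08-0.19 of the 26.4 SD. If the true fall were the halving expected in 9.1 (33.3 ng/ml), attenuation with 3 days' prolongation would be p₁ + bias/33.3, from 0.077+2.0/33.3 = 14% to 0.115+5.0/33.3 = 26%.

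A fitted mixed model weights days differently, so these figures show direction and order of size only. Nothing is computed for the ratio, because the documents give no PlGF levels.

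**The case against.** The strongest reply is that 8.2 bases the 14-day outcome on measurements made before childbirth, so the natural reading is antepartum; 6.6.1 and Table 1 are collection schedules and do not define analysis sets. That stands in part. No sentence puts post-delivery samples into the 14-day analysis. Their inclusion is inferred from sampling that runs past delivery and from the absence of any exclusion. The reply does not rescue the open-ended analysis, whose plain wording takes in everything collected, including the 6-week sample.

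A second reply is that contamination and incompleteness cannot both apply in full. That is right. If post-delivery samples count, the 14-day set is nearly complete but mixed; if they do not, it is clean but cut short by delivery. Even then, 72-78% antepartum coverage makes the completeness statement arguable for the window as a whole.

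Third, the bias figures rest on assumed levels, stay and prolongation, and 19.3 ng/ml is a normal-pregnancy value, not a post-partum one. That also stands.

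The remaining defences are weaker. Multiple imputation and the interaction test do not address delivery, and the test cannot separate a changing drug effect from unequal delivery. Section 8.2's promise to examine all data for influence on interpretation is not a pre-specified rule. A SAP is a proper place for the rule, but the documents reviewed do not contain one.

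**Conclusion.** The gap is real and should be fixed; it concerns a secondary analysis. Post-delivery samples are included by the literal wording of the open-ended analysis and are not excluded from the 14-day one. Under the stated assumptions a true 20 ng/ml fall is attenuated by about 12-20% without prolongation and about 18-36% with 3 days' prolongation. The spurious +2 to +5 ng/ml under a true null arises only if pregnancy is prolonged; with none it is zero. If only antepartum samples are meant, the completeness statement holds early in the window but not late, given about 73% delivered by day 14.

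A reader might infer that the 14-day result is certainly contaminated, that its data are mostly missing, or that the trial's main result is compromised. The documents do not support these readings: inclusion within 14 days is an inference, about 72-78% of the window is antepartum, and on 11±5 days only about 0.3-5.5% of women deliver by day 3, so the three-day primary analysis is little affected.

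**What to change.** In 9.2 and the SAP:

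1. Restrict the 14-day and longer comparative analyses of sFlt-1 and the ratio to samples drawn before delivery, with a stated rule for samples taken on the day of delivery.
2. Present post-delivery and 6-week samples descriptively by arm.
3. State that values after delivery are not imputed.
4. Report the numbers still pregnant by arm and day alongside the plots of means.
5. Qualify the completeness sentence in 8.2: about 72-78% antepartum coverage over 14 days, with about 27% of women still pregnant at day 14.

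The cost is wording and one table, settled before unblinding. The downside is fewer late samples, wider intervals in the second week, and a comparison conditional on still being pregnant, which treatment may itself affect. A sensitivity analysis for that informative truncation, such as a joint model of sFlt-1 and time to delivery, is an option rather than a requirement with at most 64 women. The primary analysis need not change on this account.

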## **2.6. Aim and objectives of a future substantive trial**

From the initial trial, we will have established:

1. The effect of pravastatin on circulating anti-angiogenic factors
2. The size of the effect that can potentially be achieved on clinically important endpoints, including pre-eclampsia severity and prolongation of pregnancy, which will be used to appropriately design and power a substantive trial
3. Clinician and patient readiness to participate in a large multi-centre trial of statins (pravastatin) in pregnancy
4. The pilot will also inform the design of a parallel study of statins in asymptomatic women, who have raised anti-angiogenic markers prior to the early onset of pre-eclampsia. The inclusion criteria for this future trial will be based on the accuracy and diagnostic thresholds of the anti-angiogenic markers, which will be established in a concurrent diagnostic study (funded separately by MRC).
5. Other information on clinical maternal and neonatal outcomes that are relevant for assessing the safety and efficacy of statins in any future trials

Should this early data suggest that statins are a promising therapy for pre-eclampsia, a larger substantive trial will be developed for symptomatic women to answer the following questions:

1. Can statins delay progression or reduce severity of early-onset pre-eclampsia and if so, how much additional gestational time can be gained?
2. Do statins improve fetal and maternal outcome?
3. What are the rates of any adverse effects to the mother or the baby?

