### **8.6. Definition of the End of Trial**

The interventional phase of the trial will end when the last participant has delivered her baby. The observational phase of the trial will cease when the 6 week follow-up has been completed for the last participant recruited.

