### **9.2.2. Proposed frequency of analysis**

- Twice yearly review of recruitment and compliance for StAmP Trial Steering Committee.
- Quarterly interim analyses of adverse events for confidential review by the DMEC for safety.
- Twice yearly review of data quality for review by the DMEC
- Main analyses of efficacy of Pravastatin once all participants have reached 6 week follow up.

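### Length of gestation is defined in days and is meant to size the next trial, but section 9.2 plans only a hazard ratio and Kaplan-Meier plots, with no estimate of days gained

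*Combined protocol and SAP*

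**What the plan says.** Section 8.2 lists the outcome as "Length of gestation post-randomisation, in days" and adds that, among secondary outcomes, "length of gestation post randomization will be considered the most important indicator of potential clinical efficacy". Section 9.2 gives its analysis: "The length of gestation (to delivery) post randomisation will be analysed using a Cox Proportional Hazards model". The outputs follow: "Hazard ratios will be calculated. Kaplan-Meier plots will be produced". The next paragraph of 9.2 deals with the remaining continuous measures, so its baseline-adjusted comparison of means does not reach this outcome. Section 9.2 also promises a point estimate with a 95% confidence interval for every result. Here that would be a hazard ratio.

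On timing, section 8.6 says "The interventional phase of the trial will end when the last participant has delivered her baby", and section 9.2.2 schedules "Main analyses of efficacy of Pravastatin once all participants have reached 6 week follow up".

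On purpose, section 2.6 says this trial will establish the achievable effect on clinical endpoints, prolongation of pregnancy among them, so that a substantive trial can be designed and powered. The first question of that later trial includes "how much additional gestational time can be gained".

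**The concern.** The outcome is measured in days and its intended use is in days, but the planned estimate is a ratio of delivery rates. The usual reason to rely on a hazard ratio alone, namely that many event times are cut off by the end of follow-up, is absent: the analysis waits until after the last delivery.

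At stake is the trial's value as a pilot for this outcome. Whoever plans the substantive trial would receive a hazard ratio and two curves, and would have to work back to days gained under assumptions that nobody had prespecified. No interval for the gain in days would exist unless it were added after the data were seen. Section 9.2 also plans no check that the hazard ratio is stable over time, which is the condition for reading it as one summary of effect.

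**Working it through.** **1. The plan's own figures.** The documents give no sample size or power for length of gestation. Section 9.1 covers sFlt-1 only, and its figures reproduce. A two-sample t-test for one standard deviation (80% power, two-sided 0.05) needs 16.7, so 17 per arm, or 34 in total. The repeated-measures factor (1 + 2 × 0.9)/3 − 0.1² = 0.923 brings this to 16 per arm, or 32 in total.

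**2. Inputs.** Recruitment is up to 64 women (9.1), allocated equally (5.3), so 32 per arm. Mean duration is 11 ± 5 days (8.2). Two assumptions are added: the ±5 is a standard deviation, since 8.2 does not label it, and the figures describe the control arm.

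**3. Does a hazard ratio fix the days gained?** For Weibull times with shape k, proportional hazards with ratio HR multiplies the mean by HR^(−1/k). So days gained = 11 × (HR^(−1/k) − 1). With HR = 0.6:

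| Shape k | Calculation | Days gained |
|---|---|---|
| 1 (exponential, SD 11) | 11 × (1.667 − 1) | 7.3 |
| 2.34 (matches mean 11, SD 5) | 11 × (1.244 − 1) | 2.7 |
| 4 | 11 × (1.136 − 1) | 1.5 |

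The same ratio spans about a five-fold range in days (7.3/1.5 = 4.9), depending on the spread of the control times.

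**4. Precision of a direct estimate.** Standard error = 5 × √(2/32) = 1.25 days. With t = 1.999 on 62 degrees of freedom, the 95% half-width is 1.999 × 1.25 = 2.5 days. If the standard deviation were 11 rather than 5, it would be 1.999 × 11 × √(2/32) = 5.5 days.

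**5. Does the choice of test matter for power?** Simulation with 32 per arm, no censoring, control mean 11 and SD 5, a mean gain of 3.5 days and 20,000 trials per row:

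| Form of the gain | t-test on days | Cox |
|---|---|---|
| Same 3.5 days for everyone, gamma | 79% | 63% |
| Same 3.5 days for everyone, normal | 79% | 71% |
| Proportional lengthening, gamma | 67% | 65% |
| Proportional lengthening, lognormal | 67% | 63% |
| Exact proportional hazards, Weibull | 66% | 70% |

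With no effect, both tests reject about 5% of the time. A run with a 3-day gain, times in whole days and Efron handling of ties gave the same pattern (t-test first): 65% against 50% for a uniform gamma shift, 54% against 53% for proportional lengthening, and 48% against 51% under exact proportional hazards.

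**The case against.** Cox regression is a conventional and valid analysis of time to delivery. It also copes with the few women who might be censored, since sections 6.5 and 8.4 let a woman withdraw consent to data collection. Calling the outcome fully observed would therefore go too far; the documents support only the absence of administrative censoring. This stands, and is why the Cox model should stay.

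The days are partly recoverable. The Kaplan-Meier plots show medians by arm, and a hazard ratio applied to the control curve yields days if hazards are proportional. Section 9.2 also defers detail to a separate SAP that is not among the documents. But a plot is not a prespecified estimate with an interval, the conversion rests on an assumption that the plan does not check, and 9.2 already names both model and estimate for this outcome.

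The explicit question about gestational time belongs to the future trial, and a hazard ratio can size an event-driven design. True, but section 2.6 makes this trial the source of the effect size on prolongation, and the outcome itself is defined in days.

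The spread is uncertain. Section 6.2.3 provides for some deliveries beyond 28 days, whereas a gamma distribution with mean 11 and SD 5 puts only about 0.5% of women there (about 0.3 of 64). A wider, skewed distribution is possible, which makes the mean less comfortable as a sole summary. This stands, and is a reason to report medians as well.

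**Conclusion.** The gap is real: the leading clinical outcome has no planned estimate in its own unit, although the data to produce one will be in hand. The hazard ratio leaves the gain open over roughly 1.5 to 7.3 days at HR 0.6, with an 11-day control mean and Weibull shapes from 4 to 1. A direct estimate would carry about ±2.5 days if ±5 is a standard deviation and all 64 women are followed to delivery, and more if the spread is wider.

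A reader might go further and infer that Cox is the wrong or weaker test, that proportional hazards is unlikely to hold, or that a comparison of means should replace Cox as the lead analysis. The documents support none of these. Cox loses materially only if every woman gains the same number of days (about 15 points with gamma times, 8 with normal times). For proportional lengthening or proportional hazards the two tests lie within about 4 points of each other, in either direction. Nothing in the documents shows which form an effect would take, so non-proportionality is a possibility to check. Section 2.4.1 also says the trial is not powered for clinical outcomes, so estimation matters more here than the choice of test.

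**What to change.** In section 9.2, and in the SAP that it promises, for length of gestation:

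- add a prespecified difference between arms in mean days from randomisation to delivery, with a 95% confidence interval;
- use the restricted mean, with the truncation time fixed in advance, if any woman is censored by withdrawal;
- report the difference in median days;
- add a check of proportional hazards;
- keep the Cox model and the Kaplan-Meier plots.

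The cost is one paragraph and one extra estimate on a secondary outcome. No new data, visits or participants are needed. The SAP should also say what the ±5 in section 8.2 is, because the expected precision depends on it.

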### **6.5.1. Time of child-birth**

Indications for child-birth is a clinical decision, which to some extent will vary between clinicians at different centres. Investigators from all participating centres have agreed that maternal indications for child-birth include uncontrollable severe hypertension (BP $\geq$ 170/110mmHg), elevated liver transaminases >500IU/L, elevated SCr >120 $\mu$ mol/L, thrombocytopaemia <50,000 or eclampsia. Fetal indications include non-reassuring CTG or worse, or reversed end diastolic flow (EDF). Lesser maternal signs may warrant child-birth if combined or if accelerating rapidly. The time that the decision was made to deliver the baby should be recorded.

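### Maternal morbidity is counted only until delivery, and five of its eight items are also delivery criteria, so a risk ratio alone mixes the rate of maternal deterioration with time at risk and the mix of delivery reasons

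*Combined protocol and SAP*

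**What the plan says.** **Outcome (protocol 8.2).** The list opens "Maternal morbidity, as indicated by serum creatinine" and runs to eight items, counted "more than 48 hours after randomisation and for the remainder of the pregnancy".

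**Delivery criteria (6.5.1).** The text says "Investigators from all participating centres have agreed that maternal indications for child-birth include uncontrollable severe hypertension" and then gives four further maternal criteria. Non-reassuring CTG and reversed end-diastolic flow are fetal indications. The same section calls delivery a clinical decision that varies between centres, and it allows delivery for lesser maternal signs.

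**Analysis (9.2).** "Dichotomous outcomes (mortality, etc) will be presented as risk ratios, with a corresponding chi-squared test performed". No time scale and no competing event is mentioned for these outcomes. Length of gestation gets a Cox model, with all deliveries pooled as events. Section 9.2 does not name maternal morbidity among the dichotomous outcomes and defers further detail to a Statistical Analysis Plan.

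Table 1 also schedules maternal morbidity until discharge and at 6 weeks, which does not match the pregnancy-only window in 8.2.

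**The concern.** When the event is often itself the reason for delivery, and delivery closes the window, the proportion of women with an event depends on two rates: how fast women reach a maternal threshold, and how fast they are delivered for something else. Treatment may change either one. A single risk ratio cannot show which has moved.

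Objective 2 in 2.5 asks about adverse or beneficial effects on the mother. Section 2.6 asks of the later trial: "Can statins delay progression or reduce severity of early-onset pre-eclampsia and if so, how much additional gestational time can be gained". Section 10.3 sends interim safety and morbidity outcomes to the DMEC. In each setting, a risk ratio near 1 could hide slower deterioration. A risk ratio above 1 could come from pregnancies that lasted longer, with no faster maternal deterioration.

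**Working it through.** **1. The plan's own figures.** The documents give no rate or power for maternal morbidity. Their sample size is for sFlt-1 (9.1), and it reproduces. A two-sample t-test with a 1 SD difference, two-sided 5% and 80% power needs 16.7, so 17 per arm = 34. The repeated-measures factor is (1 + 2×0.9)/3 − 0.1² = 0.923, and 34 × 0.923 = 31.4, so 32. The recruitment target of up to 64 gives about 32 per arm.

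**2. Overlap of 8.2 with 6.5.1.**

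| 8.2 item | On the 6.5.1 maternal list? |
|---|---|
| Creatinine ≥120 µmol/L | Yes (>120) |
| BP ≥170/110 despite treatment | Yes (uncontrollable, ≥170/110) |
| DIC and/or platelets <50 | Platelets yes; DIC no |
| Transaminase ≥500 IU/L | Yes (>500) |
| Eclampsia | Yes |
| Proteinuria ≥5 g/24h | No |
| Left ventricular failure | No |
| Cerebrovascular event | No |

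The overlap is 5 of 8 items (63%), or 5 of 9 (56%) if DIC is counted separately.

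**3. Formula for the overlapping items.** Let f be the share of placebo deliveries preceded by a maternal trigger event. Let a and b be the treatment hazard ratios for maternal triggers and for all other deliveries. With proportional cause-specific hazards, the proportion with an event by delivery is f on placebo and a·f / (a·f + b·(1−f)) on pravastatin. The documents do not give f, so 0.3, 0.5 and 0.7 are assumed, as are a and b. Example: f = 0.5, a = 0.5, b = 1 gives 0.25/0.75 = 0.333, and RR = 0.333/0.5 = 0.67.

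| Scenario | a | b | RR at f = 0.3 / 0.5 / 0.7 |
|---|---|---|---|
| Both halved | 0.5 | 0.5 | 1.00 / 1.00 / 1.00 |
| Maternal only halved | 0.5 | 1 | 0.59 / 0.67 / 0.77 |
| Maternal halved, other cut by a quarter | 0.5 | 0.75 | 0.74 / 0.80 / 0.87 |
| Other only halved | 1 | 0.5 | 1.54 / 1.33 / 1.18 |
| Maternal halved, other quartered | 0.5 | 0.25 | 1.54 / 1.33 / 1.18 |

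The last two rows have the same risk ratio, although the maternal hazard ratio is 1 in one and 0.50 in the other.

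**4. Simulation.** Inputs: 32 per arm; placebo time to delivery with mean 11 and SD 5 days (8.2), as a Weibull with shape 2.34 and scale 12.41; events counted after 48 h. Results are for f = 0.3 / 0.5 / 0.7, with ranges covering repeated runs.

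- Both hazards halved (mean gestation 11.0 to 14.8 days): chi-squared rejects in about 5 to 7% of trials at every f. The cause-specific log-rank test rejects in 30–32% / 46–47% / 59–62%.
- Maternal hazard only halved: at f = 0.5, 49% v 33% of women have an event. Chi-squared rejects in 21–22% / 28–29% / 26–28%; log-rank in 24–25% / 40–42% / 55–57%.
- Other hazard only halved: at f = 0.5, 49% v 66% have an event. Chi-squared rejects in 27–28% / 29–30% / 21%, with RR above 1 in 84–90% of trials. Log-rank stays at about 5 to 6%.

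**5. Items that are not delivery criteria.** Their difficulty is unequal time at risk. With an assumed hazard of 0.03 per day and delivery hazards halved, the risk ratio for such an item is about 1.33 if its own rate is unchanged and about 0.75 if its rate is halved.

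**The case against.** The strongest reply is that the risk ratio answers a legitimate question. If only other deliveries are delayed, more women really do experience a qualifying event (49% v 66% above), and a safety outcome should report that. This stands. A reader might infer that such a result is a false positive. It is not: it is a true difference in absolute risk, and only its attribution to faster deterioration would be wrong.

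A reader might also infer that the test says nothing about maternal deterioration. The maternal-only rows contradict that; at f = 0.3 the chi-squared test does almost as well as the log-rank test.

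Nor do the documents support saying that reaching a threshold ends the pregnancy, or that the proportion simply equals the share of deliveries on a maternal indication. Section 6.5.1 leaves delivery to clinical judgement and allows it for lesser signs, and three items are not on its list. The mechanism does not need automatic delivery, though. At f = 0.5, with only 80% or 50% of threshold events leading to delivery, halving both hazards gave 6% rejection for chi-squared against 47–48% for log-rank.

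Other planned analyses help only in part. The repeated-measures models address laboratory values and blood pressure, and 8.2 ranks length of gestation as the leading indicator of efficacy. The Cox model for gestation pools all reasons for delivery, so neither analysis resolves this outcome. Section 2.4.1 says that the trial is not powered for clinical outcomes, and the SAP is still to come. Both limit the weight of the point.

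**Conclusion.** The concern holds in limited form. As planned, the risk ratio describes how many women had an event before delivery. It cannot by itself separate a change in the rate of maternal deterioration from a change in time at risk or in the mix of delivery reasons. It is near 1 when both kinds of trigger slow equally. Under the assumed values it ranges from 0.59 to 1.54 across scenarios with the same maternal hazard ratio of 0.50.

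These sizes rest on assumed shares (0.3 to 0.7), assumed and proportional hazard ratios, and a reading of 9.2 as an ever-occurred analysis of morbidity, which is natural but not stated. Even a halving of both hazards gives the time-to-event test only about 30 to 62% power with 64 women, so the outcome remains exploratory under either analysis. A reader might conclude that the risk ratio should be replaced; the documents do not support that, since absolute risk to the mother is part of objective 2. This is a cheap improvement.

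**What to change.** In 9.2 or the SAP, for maternal morbidity:

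- Keep the risk ratio with 95% CI as the absolute-risk summary.
- Report beside it the time from randomisation to the first qualifying event, with a cause-specific Cox hazard ratio (95% CI) and cumulative incidence curves by arm. Treat delivery without a prior qualifying event as the competing event.
- State that the two are interpreted together, and give a rule for an event recorded on the day of delivery.
- State the counting window, reconciling 8.2 with Table 1.

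Morbidity indicators are already collected daily (8.3). The competing event is defined by the date of delivery, so the reason for delivery, which Table 1 does not list, is not needed. The cost is SAP wording, one extra model and two estimands to present. No clinical rule changes.
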